## **1.5 Rationale for the study**

MSF works throughout the world providing essential medical care through basic health care services, including nutritional feeding programmes and OPD clinics. Given the endemicity and magnitude of illnesses in sub-Saharan Africa, this study aims to explore the effectiveness of nutritional supplementation concurrently with an episode of one of the three key morbidities (malaria, diarrhoea and LRTI) in reducing incidence of malnutrition and recurrence of these three morbidities. If shown to be effective, MSF would consider incorporating nutritional support in its OPD protocols as supportive therapy for these infections and as a routine component of the strategy in preventing malnutrition and recurrent infection. The interventions studied are also felt to have wider relevance outside of MSF, and if results are positive, MSF will advocate to Ministries of Health, WHO and donors to include the intervention in their basic package of care.

To date there has been no evidence to show the impact of nutritional supplementation on incidence of malnutrition or morbidities amongst routine users of OPD services. In addition, there is limited information on how to roll out such an intervention, including which populations to target, the composition suitable for ill children and the preferred form of delivering such supplements.

Though RUTF is a standard fortified food product seen in many MSF interventions, it is a logistically heavy product (i.e. cost, bulk and weight). The question remains as to whether it is essential to include the macronutrient

components (incl. energy and proteins) of RUTF. It is not evident that macronutrients are necessary to prevent malnutrition in children with disease, as anorexia is modulated by micronutrients. It is important from a cost effectiveness perspective to investigate whether micronutrients alone would prevent malnutrition in ill children. For this reason, two commonly used supplements will be investigated, i.) an RUTF with both macro- and micronutrients and ii.) a powder with only the multi-micronutrient component.

The duration of the supplementation should cover the period to recover from weight loss and disease. A study from Gambia suggests that recovery from weight loss for diarrhoea occurs within the first 14 days [10]. In addition, 14 days will cover convalescence from disease. Finally 14 days is an operationally feasible intervention.

While timely and appropriate treatment of disease is the priority, a nutritional supplement for a short duration (14 days) as a complimentary therapy might have an impact on the incidence of illnesses. The aim of this study is to assess whether nutritional supplementation will significantly reduce both the incidence of malnutrition and the incidence of the three main childhood illnesses. If successful, this may prevent subsequent illness and break the vicious cycle of dependence between malnutrition and disease.

## 2. STUDY OBJECTIVES

**The aim of the study is to** “To determine the *effectiveness* of 14 days nutritional supplementation (RUTF or MNP) given concurrently with the appropriate medical treatment, in children diagnosed with malaria and/or diarrhoea and/or LRTI in reducing the incidence of acute malnutrition and the incidence of the three study diseases compared to a control group.”

**The primary objective** is to determine the effectiveness of 14 days of RUTF supplementation versus no supplementation control group on the *incidence of acute malnutrition*

**Primary Hypothesis:** Supplementation for 14 days with RUTF, concurrent to appropriate medical treatment for malaria, and/or LRTI, and/or diarrhoea reduces the incidence of acute malnutrition compared to a control group during 6 months follow-up, amongst children 6-59 months of age with malaria and/or, LRTI and/or diarrhoea at time of recruitment.

**Secondary objectives** include:

Incidence of malnutrition

- i.) Determine the efficacy of 14 days MNP supplementation versus a control group and RUTF versus MNP on the incidence of acute malnutrition during 6 months follow-up,

Frequency of morbidity

- ii.) Determine the effect of 14 days supplementation on the *frequency of morbidity* (3 study diseases) during 6 months follow-up, comparing both intervention groups to the control group and comparing RUTF to MNP)

Weight changes immediately after intervention period, measured at day-14 and day-28

- iii.) Measure *mean weight change* (total change and rate (grams/kg/day) of change), comparing both intervention groups separately (RUTF and MNP) to control group
- iv.) Determine *frequency of ‘no weight gain and/or weight loss’*, comparing both intervention groups separately (RUTF and MNP) to control group
- v.) Assess if provision of 14 days of RUTF or MNP supplement promotes a sustained weight gain, measured after 28-days of follow-up, comparing both intervention groups separately (RUTF and MNP) to control group

Sub group analyses

- vi.) Children under 3 years of age at inclusion: Determine the effect of 14 days supplementation on the *incidence of acute malnutrition* and *frequency of morbidity* (3 study diseases) during 6-months follow-up, comparing children under 3 years of age to older children.
- vii.) Breastfed children: Determine the effect of 14 days supplementation on the *incidence of acute malnutrition* and mean weight gain (incl. rate) during 6-months follow-up, comparing breastfed children to those not breastfed.

### **3. STUDY DESIGN**

This is a randomized controlled trial with three study groups. Children 6 to 59 months of age presenting at the OPD in Kaabong Hospital Kaabong district, Karamoja region and diagnosed with one or more of the three study diseases (malaria, diarrhoea and LRTI) are eligible for the study.

Children participating in this study will be randomised to one of the three groups to:

- A) Receive 14 days of RUTF supplementation with standard care and treatment or
- B) 14 days MNP supplementation with standard care and treatment
- C) Be included in a control group receiving standard care and treatment but not receiving nutritional supplementation (control group)

Individual follow-up will be 6 months. During this time, children in the RUTF or MNP group will receive 14 days nutritional supplement every time diagnosed with at least one of the three study diseases, not exceeding more than 14 days supplementation in any 28 day period.

### **4. STUDY SITE**

The study site is a MoH/MSF Paediatric OPD\* located in Kaabong Hospital. Karamoja, Uganda, where MSF will provide support in diagnoses and treatment. This site was selected among other MSF programmes taking into account different factors: pastoral and agricultural population, food security, food consumption, diet composition, food sources and high incidence of diseases such as malaria, diarrhoea and LRI [35]. The aim of the study is to assess whether nutritional supplementation will significantly reduce both, the incidence of malnutrition and the incidence of the three main childhood illnesses. If successful, this may prevent subsequent illness and break the vicious cycle of dependence between malnutrition and disease.

#### **4.1 Number of Participants**

The total study population will consist of 2,202† participants, 734 per study group. All children will be recruited at one study clinic site. The study team is expected to recruit approximately 15 participants per day, requiring approximately 143 working days (approximately 29 weeks based on a 5-day work week) for recruitment.

#### **4.2 Inclusion criteria**

Children will be included if they meet all the following inclusion criteria:

- 6 to 59 months of age
- Not malnourished children
- Diagnosis of malaria and/or diarrhoea and/or LRTI
- Intending to remain in area for the duration of the 6 month follow-up
- Living within approximately 60 minutes walking distance from the clinic
- Informed consent from a guardian\*

\* Parent or other legal guardian. If not a parent, must be at least 18 years of age

#### **4.3 Exclusion criteria**

Children will not be included if they meet any one of the following exclusion criteria:

- Child is exclusively breastfeeding
- Child is acute malnourished
- Presence of 'General Danger Signs'
- Presence of severe disease (including severe malaria, severe LRTI, severe diarrhoea)
- Needing hospitalisation for any reason
- Known history of allergy to the nutritional supplementation
- Having a sibling enrolled in the study\*

---

\*Until March 2010 MSF was supporting the MoH structure with on the job training for MoH staff.

† \*Information on the determination of the sample size is elaborated in section 9.1

\*When one twin child is recruited, the twin sibling cannot be recruited but will receive the same supplement. This is done to limit the risk that, given the unique nature of twins, a guardian may share supplementation with twin siblings.

Patients who do not meet all eligibility requirements and/or who fulfil any one exclusion criteria at screening will be considered not eligible for participation (See Annex f1-screening form).

## **5. PARTICIPANT SELECTION AND ENROLMENT**

### **5.1 Identifying participants**

Study patients will be recruited from amongst routine users of the Kaabong OPD services. Initial diagnosis of the study diseases will be conducted at the Paediatric OPD using MoH/MSF clinical diagnostic tools and protocols.

Patients diagnosed with one of the 3 study diseases at the OPD will receive drug prescriptions as needed, a brief explanation about the study, and be voluntarily referred to the study clinic for further screening for study inclusion.

### **5.2 Consenting participants**

Guardians of the participants will be informed about the purpose of the study, the procedures involved when participating, and asked for their consent. The parent or guardian of the child must be older than 18 years of age to give consent.

Informed consent forms will be translated into local languages, back-translated and piloted for comprehension in the area of the study site. As a significant proportion of the population is not literate, the consent form will be read out to the patient's guardian to obtain oral consent as required (see annex f2-informed consent). Participants will receive a copy of the consent form for their reference

It will be explained to the guardian that participation is voluntary and that patients will receive the same standard of medical treatment whether or not they agree to participate in the study. It will be further explained that patients can discontinue participation from the study at any time without explanation and without any negative impact on their future care and treatment.

### **5.3 Screening for eligibility**

After referral to the study clinic, patients will be further informed about the study and screened by the study team.

A maximum daily number of children accepted for study screening will be defined according to the capacity of the study team. Based on information of how many OPD referrals the study team can expect per day, children referred will be selected systematically for further screening. As an example, if the study team can screen at most 30 children per day and they expect that 60 children will be referred to the study clinic from the OPD, every 2nd child will be screened for study inclusion. Selection for screening will be in the order of presentation to study clinic after referral from the OPD.

If the child is deemed eligible for the study according to inclusion and exclusion criteria, the guardian will be asked to voluntarily participate.

### **5.4 Ineligible and non-recruited participants**

With limited screening capacity and a high volume of OPD patients with at least one of the study diseases, some children referred from the OPD to the study clinic will not be screened. If a child is not to be screened, the guardian will be informed of this immediately and be referred back to the MoH OPD to attain follow-up care or medications as per normal OPD protocol. This child will receive no further services from the study clinic.

## **6. RANDOMISATION**

### **6.1 Randomisation**

Simple randomisation will be implemented. There will be no reference to assigned study groups (e.g. no use of terminology such as group A, B, or C). Rather, the total patient numbers will be randomly allocated to an equal proportion of one of the three groups.

The randomization list will be computer generated by a statistician.

## **6.2 Blinding**

Owing to the nature of the product packaging and use of a control group without placebo study participants will not be blinded to which study group they were assigned. It will also not be possible to blind staff distributing the supplement.

Study staff blinded to the allocation treatment includes:

- Principle investigator
- Co-investigators
- Field Research Coordinator
- All clinical and ancillary medical staff
- Technical staff collecting anthropometric measurements
- Questionnaire interviewers
- Data managers
- Statisticians

Every effort will be made to ensure that study staff remains blinded to the treatment allocation. Efforts will be made to inform participants and staff to avoid discussion that might reveal allocation.

The allocation scheme will be formally revealed only after the data from the last participant has been captured.

Each participant will be assigned a unique study identification number, used to identify the study participant in all procedures. Study numbers will be assigned sequentially as subjects enter the study. Once a number has been assigned, that number will not be used again (e.g. if a subject discontinues or a number is allocated incorrectly).

## **6.3 Treatment allocation**

The study dispenser\* will have access to a register with all unique study numbers and the assigned intervention. The study dispenser will allocate the study group to the participant when the participant collects the nutritional supplement. As such, the dispenser will be the only person of the study team to know the allocation scheme. The allocation register will be kept by the dispenser in such a manner that guarantees no unauthorized staff can have access. (see annex f9-dispensary allocation register)

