## **7.3 Control group**

For the purpose of this study, it is not practically feasible to design and manufacture a placebo for RUTF or the MNP. Children randomly assigned to the control group will receive equivalent care and follow-up as the children assigned to a study group receiving supplementation. The only difference is that they will not receive a nutritional supplement (current clinical practice does not include nutritional supplement).

---

\*One nurse assistant will be selected as study dispenser/treatment allocation (always will be the same person). The paragraph refers to randomization. It is only highlighting that no one except one individual will have access to the list in order to avoid anyone influencing the randomization of patients to treatment.

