**Repeated supplementation:** Patients presenting with a new episode of a study disease will receive a new 14-day supplement, according to the intervention originally assigned. Though care and treatment will be available whenever ill, a child will not receive more than 14 days supplementation within any 28 day period. For example, a child receiving a new supplementation package on day-42 due to a newly diagnosed study disease cannot receive another supplementation package before day-70.

One reason to limit the distribution to a monthly frequency is to minimize potential bias related to the likelihood that children receiving Plumpynut® (a product known and recognized by the community) may be more likely to come forward for an unscheduled visit with the intention to receive additional distribution of supplementation.

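### One on-site dispenser holds an open register of every study number and arm, including children not yet enrolled, and the protocol describes neither a hidden sequence nor an independent check during the trial

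*Protocol*

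**What the plan says.** Section 6.1: "The randomization list will be computer generated by a statistician". Randomisation is simple, to three equal groups.

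Section 6.2: "Study numbers will be assigned sequentially as subjects enter the study". A number once given is not used again. The investigators, the field research coordinator, clinical staff, measurers, interviewers, data managers and statisticians are listed as blinded. Participants and the staff who distribute supplements cannot be. The scheme is formally revealed only once the last participant's data are in.

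Section 6.3: "The study dispenser\* will have access to a register with all unique study numbers and the assigned intervention". It continues: "The study dispenser will allocate the study group to the participant when the participant collects the nutritional supplement". The dispenser keeps this register and is described as the only member of the study team who knows the scheme.

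The footnote on the dispenser (printed under section 7.3) says: "One nurse assistant will be selected as study dispenser/treatment allocation (always will be the same person". It gives the reason for single custody: "It is only highlighting that no one except one individual will have access to the list in order to avoid anyone influencing the randomization".

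Section 8.5 has the same dispenser count and record the returned sachets, after the first 14 days only. Section 8.2 (repeated supplementation) anticipates that "children receiving Plumpynut® (a product known and recognized by the community) may be more likely to come forward" for extra visits. Section 10.1 sets out quality control by the field research coordinator but names no check of dispensing against the list.

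**The concern.** Allocation concealment means that nobody in contact with recruitment can learn the next assignment before the child is irrevocably in the trial. A register that shows all numbers with their arms, combined with sequential numbering, gives that knowledge to one person at the site for the whole of recruitment. The stated safeguard stops other people from looking. It neither restrains the holder nor lets anyone else verify what the holder does.

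Two things raise the stakes. The trial has no placebo and is open at the dispensary, so the arm is obvious at hand-over. And the protocol itself expects demand for one of the products. If upcoming arms reached those who screen, or guardians, the groups could differ at entry. If the product handed over differed from the listed one, the contrast between groups would shrink.

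**Working it through.** **What the register holder knows.** Without the list, a person guesses the next arm correctly one time in three under equal allocation to three groups. With an open register and sequential numbers, the holder is right every time, for all 3 × 734 = 2,202 assignments.

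**What the holder can do with it.** Setting the sections side by side:
- Screening follows order of presentation (5.3), numbers follow order of entry (6.2), and the child meets the dispenser when collecting the supplement (6.3). No section gives the dispenser a screening, consent or numbering role, so the dispenser does not choose which child gets which number.
- Two routes remain. Route A: the dispenser passes upcoming arms to screeners or guardians, which is selection bias. Route B: the dispenser hands out a product other than the listed one, which is crossover.
- For both routes, I looked for something in the text that would prevent or detect them during the trial. Section 6.3 protects the register from other staff only. The sachet count in 8.5 is done by the dispenser. The coordinator who reviews records under 10.1 is blinded. Serious adverse event reports carry the study group (11.6), but only for single events. No independent reconciliation is described.

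**Size of route B.** Inputs from section 9.1: 660 per group, rates 0.20 (control) and 0.14 (RUTF), two-sided 0.05, 80% power.

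The plan's own figure first, using the Poisson regression formula with a binary covariate at proportion 0.5:

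N = (1.96·√V0 + 0.8416·√V1)² / (0.20·(ln 0.7)²), with V0 = 4 and V1 = 2 + 2/0.7 = 4.857.

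This gives N = 1311, against 1320 stated. Allowing for 10% drop-out, 660/0.9 rounds up to 734 per group. The sample size reproduces, and this point does not affect it.

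For the effect of crossover I used a Wald test on the log rate ratio:

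SE = √(1/(660·r0) + 1/(660·r1)), power = Φ(|ln(r1/r0)|/SE − 1.96).

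With no crossover, SE = √(1/132 + 1/92.4) = 0.1356, and power = Φ(0.3567/0.1356 − 1.96) = 74.8%. This is below 80% because the Wald form is more conservative than the plan's formula; only the change within the table matters.

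If a share f of listed controls receives RUTF and children are analysed in their listed arm, the control rate becomes r0 = 0.20(1 − f) + 0.14f. The protocol gives no value for f, so a range is shown:

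| f (assumed) | r0 | Expected rate ratio | Power |
|---|---|---|---|
| 0 | 0.200 | 0.70 | 74.8% |
| 5% | 0.197 | 0.71 | 70.9% |
| 10% | 0.194 | 0.72 | 66.6% |
| 20% | 0.188 | 0.74 | 57.4% |

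With no true effect, crossover analysed by listed arm leaves the error rate at 5%.

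**Size of route A.** The documents give no figure from which to derive it.

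**The case against.** The strongest defence is that the design already separates the list from enrolment. Those who screen, number, measure and treat are blinded, and the dispenser meets a child who already has a number. Steering a particular child into a particular slot would need collusion at about 15 enrolments a day (4.1). The register form is in an annex that is not shown, and it may contain controls. All of this stands. It narrows the routes to bias without closing them, and an open list of future assignments remains an avoidable exposure.

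A reader might infer four stronger things that the documents do not support.

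- **That upcoming arms are known at the site at large.** Section 6.2 lists all other study staff as blinded; one person knows.
- **That nothing planned could reveal steering.** Section 9.3 plans pairwise baseline comparisons with a check of clinical relevance, and 9.3.2 plans further adjustment, including for age, underlying illness and socio-economic factors, where baseline values differ. The statistician's list also exists apart from the register and could be compared with it at the end.
- **That the false-positive rate is inflated.** That needs leaked arms or a falsified register, plus systematic swapping by risk. As a pure hypothetical, suppose there is no true effect and 5% to 10% of each arm is swapped, with children at 1.5 to 2 times the base rate placed in RUTF and children at 1/1.5 to 1/2 of it placed in control. The rate ratio would be 1.04 to 1.16, and the rejection probability about 6% to 22.5%. None of these inputs comes from the protocol.
- **That the text on statisticians contradicts itself.** A statistician generates the list while statisticians are listed as blinded, but a list generator outside the study team satisfies 6.1, 6.2 and 6.3 together. A clarification would be enough.

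**Conclusion.** The point holds as a weakness in allocation concealment, not as evidence of bias. One on-site person can see all 2,202 assignments in advance, dispenses the product and counts the returns. The text shown describes no hidden sequence and no independent reconciliation before the scheme is revealed.

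The calculable consequence, dispensing against the list, is modest: 5% of controls receiving RUTF costs about four percentage points of power (74.8% to 70.9%). This assumes 660 per group, the plan's rates, analysis by listed arm and crossover unrelated to risk. Leakage of upcoming arms could do more harm, but it is neither described nor quantifiable from the protocol. The change is worth considering because it is inexpensive and concealment cannot be restored once recruitment is over.

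**What to change.** In section 6.3, replace the open register with sequentially numbered, opaque, sealed envelopes, one per study number, prepared off site from the existing computer-generated list. Each is opened only after the child with that number has been enrolled and has completed baseline measurements, and the date and arm are recorded on the slip. The dispenser then keeps only the record of numbers already opened, which repeat supplies require.

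The master list stays off site with the list generator, or with another existing person who has no role in recruitment, measurement or analysis. That person periodically compares opened slips and dispensing records with the list. This step is needed as well as the envelopes: they conceal future arms, but only reconciliation detects a product handed out against the assignment.

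In 6.1 or 6.2, add a sentence saying that the statistician who generates the list is not the one who analyses the trial.

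Cost: a short amendment to 6.1 to 6.3, preparing and handling about 2,202 envelopes, and a recurring list check. No extra children or visits are needed.
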